***4.5 Clinical and Laboratory Assessments***

Blood pressure measurements, blood for serum cholesterol and thomboxane estimation will be collected at the end of the study.

**Blood Pressure**

Seated blood pressure will be measured using an electronic sphygmomanometer and an appropriately sized cuff on the right arm of participants. Two readings will be taken and the mean calculated.

**Blood samples**

Serum cholesterol measurements are usually routinely available in patients on lipid lowering treatment and these will be recorded at baseline. A venous blood sample, identifiable by the participants unique study number and the time and date when the sample was taken, will be collected at the 6 month follow-up visit and spun to provide serum for analysis of total cholesterol, HDL cholesterol, triglycerides and calculated LDL cholesterol.

**Other measurements**

Each patient will be questioned at the end of the study to assess non-adherence to their combination therapy prescribed at the start of the trial. Adherence will be assessed by asking the patient the following questions:

1) Are you still taking your i i) Cholesterol lowering drug (eg. statin) ii) Blood pressure lowering drug? (eg. lisinopril)

2) In the past month were there any days when you did not take your medication?

3) If so, how many days did you not take your medication?

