**Appendix E Text 23**

**Appendix F Letter 24**

**1. INTRODUCTION**

***1.1 Abstract***

A randomised controlled trial of text message reminders will be conducted in 300 patients who are receiving combination therapy with at least one lipid lowering drug (eg. a statin) and/or one blood pressure lowering drug (eg. an ACE-inhibitor). The intervention arm will consist of a “Text Message Programme” – periodic text messages asking whether patients have taken their medication, adapted, over time in their frequency, to the responses received, coupled with telephone or clinic follow-up to resolve reasons for non-adherence. The control group will receive standard care. Non-adherence to therapy (discontinuing one or more of the starting combination) will be assessed at 6 months by questionnaire. Serum cholesterol and blood pressure measurement will be undertaken as independent, objective measures of drug use. Allowing for a 20% loss-to follow up, the study has 80% power to identify a statistically significant reduction in non-adherence of 50% in the intervention group at a 0.05 level of statistical significance.

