***1.2 Background***

Coronary heart disease (CHD) is the leading cause of death in both developed and developing countries.1 Approximately one third of all deaths are due to CHD in England and Wales.2

Combination drug therapy with antiplatelet, blood pressure and serum cholesterol lowering drugs is effective in reducing the risk of first cardiovascular disease events; about ¾ of all heart attacks and strokes could be prevented with complete adherence to treatment.

Non-adherence to medications is however common for patients with cardiovascular diseases and greatly reduces the preventive effect. Jackevicius and colleagues found that about one quarter of all patients with a history of myocardial infarction stopped their cardiac medications within 1 week of discharge from hospital3 and more than half had discontinued statin therapy two years later.4 Newby and colleagues found that less than half of patients with angiographically confirmed coronary artery disease remained on statins one year after starting treatment in hospital (44% non-adherence) and 79% of patients who had been prescribed the three required classes of preventive therapy (antiplatelet therapy, lipid lowering therapy and blood pressure lowering therapy) stopped at least one class of drug after one year.5 The levels of non-adherence may be under-estimated in these studies, based as they were on prescription re-fills and self-reported continuation on treatment, rather than objective measures (blood or urine tests) of drug intake.

Non-adherence to medical treatment is also a major health-economic problem. An estimated £100 million is wasted each year in Britain because of unused prescribed medications6. Reasons for non-adherence include side-effects of treatment, a belief that treatment is not-required, not remembering to take treatment, loss of interest in prevention when treatment has no perceptible benefit, and loss of contact with the prescribing medical team over time7. A recent publication from the National Institute for Health and Clinical Excellence called for interventions to improve the extent to which patients remain on effective medication for chronic conditions such as coronary heart disease8, which cost the NHS about £500 million in 2009.9 Non-adherence to cardiovascular medication therefore has a personal and economic impact.

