**Phase 1**

**Phase 2**

**Phase 3**

**Week 1-2**

**Week 3-4**

**Weeks 5+**

**End of study**

Patients receive a daily text message for the first 2 weeks of the study (*Phase 1*), every alternate day for the second 2 weeks of the study (*Phase 2*), and weekly thereafter (*Phase 3*).

The wording of the text messages will vary according to the phase of the TMP protocol. An example of the daily text massage reminder is:

‘***Hello Mr/Mrs……. Have you taken your heart medication today? Please text back “Y” if the answer is Yes, I took my medication before receiving this text”, “P” if the answer is “Yes, the message prompted me to take my medication” and “N” if the answer is “No”. Thank you. From The Barts and The London Heart Team***’.

Any non-responders or patients who reply back ‘NO’ in response to the message will receive a telephone call form the study coordinator, to determine whether the patient is experiencing problems taking their medication, and resolve this if possible (e.g. the patient has run out of medication or they have been abroad).

If specialist advice is needed (e.g. whether symptoms may be a side-effect of treatment) participants will be informed that they will be contacted by a study pharmacist or doctor within the next few days. If the problem can not be resolved over the phone the patient will be advised to make an appointment with their GP. A letter will be sent to the patient’s GP summarising the problem with their medication and a copy of this letter will be sent to the patient’s home address.

If patients can not be contacted by telephone, a letter will be sent to their home address informing them that we have been unable to contact them by telephone and asking them to contact the study team (Appendix B).

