**** possible additional assessment, if practical***

**5.** **STUDY ENDPOINTS**

***5.1 Primary end-point***

The primary endpoints are:

1. Continuation rate: The proportion of patients in each arm remaining on combination therapy at the end of follow-up.*
2. Number of days in the last month of the study that patients missed taking their medication.

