**6. STATISTICAL CONSIDERATIONS**

***6.1 Number of Participants***

The TMP is expected to reduce non-adherence by 50%. Non-adherence among patients with angiographically confirmed coronary artery disease has been reported to be at least 50%3. To be conservative we have taken the non-adherence rate in the control arm to be 30%. A study of 300 participants would have 80% power to detect a 50% reduction in non-adherence at the 5% level of significance. This allows for a 20% loss-to-follow up.

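### Both primary endpoints are unblinded self-report, only the TMP arm is texted and telephoned about missed doses, and nothing separates or blinds the questioner, so arm-dependent under-reporting could favour the TMP

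*Protocol*

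**What the plan says.** **Outcome.** Protocol 5.1 names two primary endpoints: the proportion still on combination therapy at the end of follow-up, and the number of days missed in the last month. Both come from three questions listed in 4.5 under Other measurements, where "Each patient will be questioned at the end of the study to assess non-adherence". The Follow-up Visit text in 2.4 places this at a clinic visit 6 months after randomisation, and the flow diagram labels the outcome as self-reported. The Abstract (1.1) says non-adherence "will be assessed at 6 months by questionnaire".

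**Contact with one arm.** Under the algorithm in 2.4, TMP patients are texted daily for two weeks, on alternate days for two weeks and weekly after that. Those who answer No or do not answer "will receive a telephone call form the study coordinator". The GP letter (Appendix B) has a study doctor or pharmacist making the call. Controls receive standard care.

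**Who records.** Section 7.2 makes the study investigators responsible for the case report form. No section names an independent or allocation-blind questioner.

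**Other measures.** Cholesterol and blood pressure are required at follow-up in both arms. The Abstract presents them as objective indicators of drug use, and 5.2 lists them as secondary endpoints. Hair is stored for possible future analysis (4.5). Refill ascertainment is on the schedule in 4.6 but is marked "possible additional assessment, if practical". On earlier adherence studies, the Background (1.2) remarks: "The levels of non-adherence may be under-estimated in these studies, based as they were on prescription re-fills and self-reported continuation on treatment".

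**The concern.** Patients cannot be blind to text messages. For six months one arm is asked much the same question as the outcome question, and learns that admitting a missed dose, or staying silent, brings a call. That arm is then asked about adherence in person. Some TMP patients may give the answer that seems to be wanted, and controls have had no comparable experience.

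Under-reporting that is equal in the two arms lowers both rates and does not create a false difference where there is none. Under-reporting that is greater in the TMP arm does create one, in the direction the trial hopes to see. More patients would not cure it, because it is bias and not imprecision.

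The interpretation of a positive primary result is at stake. No required measure in the protocol checks an individual patient's answer, and the scheduled refill record may be obtained for only some patients, or unequally by arm.

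**Working it through.** **Inputs from the protocol.** Section 6.1 gives 30% control non-adherence, a 50% reduction (to 15%), and 20% loss to follow-up: "A study of 300 participants would have 80% power to detect a 50% reduction in non-adherence at the 5% level of significance". Allocation is 1:1 (4.4), so the evaluable number is 300 × 0.8 / 2 = 120 per arm. Sidedness is not stated; a two-sided test is assumed.

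**Input not in the protocol.** The share u of TMP non-adherers who report themselves adherent is an assumption, so a range is shown.

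**Step 1: exposure of the TMP arm.** Over 26 weeks, 14 daily + 7 alternate-day + 22 weekly (weeks 5 to 26) = about 43 messages. Controls receive none.

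**Step 2: reproduce the plan's own figure.** With pooled proportion 0.225 and no continuity correction,

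n per arm = [1.96·√(2 × 0.225 × 0.775) + 0.8416·√(0.30 × 0.70 + 0.15 × 0.85)]² / 0.15² = (1.1575 + 0.4889)² / 0.0225 = 120.5, rounded up to 121.

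The total is 242, and 242 / 0.8 = 303, against the stated 300. Power at 120 per arm is 79.8%. The sample size reproduces.

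**Step 3: no true effect, under-reporting in the TMP arm only.** True non-adherence is 30% in both arms. Observed rates are p1 = 0.30 (control) and p2 = 0.30 × (1 − u) (TMP). With d = p1 − p2, p̄ = (p1 + p2)/2, SE0 = √(2p̄(1 − p̄)/120) and SE1 = √((p1(1 − p1) + p2(1 − p2))/120),

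P(significant, favouring TMP) = Φ((d − 1.96·SE0)/SE1).

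For u = 20%: p2 = 0.24, p̄ = 0.27, SE0 = 0.0573, SE1 = 0.0572, so Φ((0.06 − 0.1123)/0.0572) = Φ(−0.915) = 0.18.

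| u in TMP arm | Observed control vs TMP | P(significant, favouring TMP) |
| --- | --- | --- |
| 0% | 30% vs 30% | 2.5% |
| 10% | 30% vs 27% | 7.4% |
| 20% | 30% vs 24% | 18% |
| 30% | 30% vs 21% | 36% |
| 40% | 30% vs 18% | 59% |
| 50% | 30% vs 15% | 80% |

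At u = 50% the whole planned effect appears with no real benefit.

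**Step 4: controls under-report too.** With a 20-point excess in the TMP arm the probability is 19% (10% vs 30% hidden), 21% (20% vs 40%) and 23% (30% vs 50%). With 10% hidden in both arms it is 2.5%. The problem therefore needs a difference between arms, not perfectly candid controls.

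**Step 5: in patients.** Against 36/120 non-adherent controls, 22/120 in the TMP arm gives a difference of 14/120 = 0.1167, pooled proportion 58/240 = 0.2417, standard error 0.0553 and z = 2.11. With 23/120, z = 1.95, just short of 1.96. So 14 misreporting patients of 36 (39%) would suffice.

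**Step 6: a real but smaller effect.** If the true reduction is 20% and 20% of the remaining TMP non-adherence is hidden, the observed rate is 0.30 × 0.8 × 0.8 = 0.192. That reads as a 36% reduction.

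Nothing was computed for days missed, because the protocol gives no distribution for it. It comes from the same questioning, so the same mechanism applies.

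**The case against.** Several counter-arguments have force.

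- **The questioner.** A reader might infer that the staff who texted and telephoned also ask the outcome questions. The protocol does not say so. The coordinator telephones, investigators complete the form, and the questioner is not identified. What stands is that no separation or blinding is specified.
- **Objective measures exist.** Cholesterol and blood pressure are mandatory in both arms, and hair is stored. It would be wrong to call refills the only scheduled information that does not depend on the patient's word. A reported gain with no movement in cholesterol or blood pressure would be suspect. A reader might add that these measures are too imprecise at this size to help, but the protocol gives no standard deviation or expected difference, so that cannot be claimed from it. What stands is that they work at group level, do not measure missed days and do not enter the adherence endpoint.
- **Refills are imperfect.** The Background places refills alongside self-report as possibly under-estimating non-adherence. The intervention may also prompt refills directly, since calls deal with patients who have run out of tablets. Refills are therefore a partial check.
- **Direction and size are assumed.** TMP patients, asked often and helped when they answer No, might admit missed doses more readily. Equal under-reporting does no harm to the error rate. Both points are fair, and the percentages show vulnerability, not a forecast.
- **Questionnaire versus questioning.** These do not contradict each other, because a questionnaire can be read out by staff. The mode is simply not fixed.

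**Conclusion.** The point holds as a weakness of outcome ascertainment. Both primary endpoints are unblinded self-report, contact about missed doses is confined to one arm, and the protocol neither separates nor blinds the questioner. If under-reporting is greater in the TMP arm, the chance of a spurious result favouring the TMP rises from 2.5% to about 18%, 36% and 80% when 20%, 30% and 50% of TMP non-adherence is hidden. These figures assume no true effect, 30% non-adherence, 120 per arm, a two-sided 5% test and under-reporting in the TMP arm only.

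A reader might go further and conclude that a positive result could never be told apart from reporting bias. The documents do not support that, because cholesterol and blood pressure offer some corroboration at group level. Nor is the sample size in error. The change is a low-cost improvement that should be made.

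**What to change.** **Outcome questions.** In 2.4 (Follow-up Visit) and 4.5 (Other measurements), state that the same three questions are answered on a written form, which the patient completes alone before seeing study staff. Have it entered by existing staff who are not told the arm. This also settles the mode of administration.

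**Refill data.** In 4.6, remove the wording that makes refill ascertainment optional and require it by the same method in both arms. Add it to 5.2 as a supportive secondary endpoint. Describe it, together with cholesterol and blood pressure, as a partial check on the primary result and not as verification of it.

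**Cost.** A printed form and routine record requests, with no additional assessor. Some answers will be unclear or missing that staff could have clarified on the spot. Patients still know which arm they were in, so respondent bias is reduced and not removed; masked entry deals only with bias in recording.

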****NB:***

***If the patient started on two classes (e.g. lipid lowering plus blood pressure lowering) and is taking only one (e.g. lipid lowering) at follow-up they would be non-adherent.***

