***If the patient started on one class (eg. lipid lowering) and is taking none at follow-up they would be non-adherent.***

***If patients change drugs within the same class they would remain adherent.***

***i.e. if the starting treatment included lipid lowering (simvastatin) and blood pressure lowering (lisinopril) and the follow-up regimen included atorvastatin (lipid lowering) and losartan (blood pressure lowering), then the patient would have adhered to starting regimen.***

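### The missed-days primary endpoint does not say which drugs it covers, so a patient who stopped one of two classes may score zero days or a full month

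*Protocol*

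**What the plan says.** Section 4.5 (Other measurements) introduces the follow-up questions as a means "to assess non-adherence to their combination therapy prescribed at the start of the trial". Three questions follow.

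- Question 1 asks whether the patient is still taking each class, listed separately: "Cholesterol lowering drug (eg. statin) ii) Blood pressure lowering drug? (eg. lisinopril".
- Question 2 does not mention class: "In the past month were there any days when you did not take your medication".
- Question 3 follows only if question 2 is answered yes, and asks for one number: "If so, how many days did you not take your medication".

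Section 5.1 lists two primary endpoints. The first is "Continuation rate: The proportion of patients in each arm remaining on combination therapy at the end of follow-up", marked with an asterisk. The second is "Number of days in the last month of the study that patients missed taking their medication", without an asterisk. The note that the asterisk points to says that a patient who started on two classes and "is taking only one (e.g. lipid lowering) at follow-up they would be non-adherent". It says that a patient who started on one class and "is taking none at follow-up they would be non-adherent".

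Section 3.1 expects most patients to be on both classes, without giving a figure. Section 6.1 bases the sample size on non-adherence of 30% in the control arm and a halving of it.

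**The concern.** The same questionnaire is specific to class for one primary endpoint and not for the other. The continuation endpoint has a defined reference regimen (what the patient started on) and a rule for dropping part of it. The missed-days endpoint has neither. A patient on two classes who gave up the blood pressure drug and takes the statin every day can answer no to question 2 in good faith. Question 3 is then skipped and the count is zero. Another patient with identical behaviour, thinking of everything first prescribed, reports every day as missed.

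At stake is what the second primary endpoint measures. Identical drug-taking can be scored at either end of the scale, in the patients whom the intervention is meant to help. If many of them answer for the remaining drug only, the endpoint loses much of the contrast between the arms.

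**Working it through.** **1. The Protocol's own figure.** Section 6.1 states 300 participants, 80% power, a 5% level, 30% v 15% non-adherence and 20% loss to follow-up; section 4.4 gives 1:1 allocation. A two-sided test is assumed. With the pooled-variance formula, the mean proportion is 0.225 and

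n per arm = [1.96 × √(2 × 0.225 × 0.775) + 0.842 × √(0.30 × 0.70 + 0.15 × 0.85)]² / 0.15² = 121 (rounded up).

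Dividing by 0.8 gives 152 per arm, or 304 in total. Conversely, 150 × 0.8 = 120 evaluable patients per arm give 79.8% power. The stated figure reproduces. It concerns the proportion non-adherent, so it belongs to the continuation endpoint; no calculation is given for missed days.

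**2. The two endpoints side by side**, assuming a 30-day month and stopping before that month began:

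| Patient | Continuation | Missed days, if the question means the starting regimen | Missed days, if it means drugs now taken |
| --- | --- | --- | --- |
| Started two classes, stopped one, takes the other daily | Non-adherent | 30 | 0 |
| Stopped everything | Non-adherent | 30 | Not defined |
| Still on both, skips only one of them on some days | Adherent | One count, class unknown | One count, class unknown |

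The first row is the main problem. In the last row the two readings coincide, but it is still unstated whether a day with one of two drugs taken counts as missed, and the form cannot show which class was skipped.

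**3. Effect on the between-arm difference (illustration).** Inputs from section 6.1: 30% and 15% non-adherent. Assumptions that are not in the Protocol: all of these patients stopped for the whole 30-day month, other patients add no missed days, and a share f of stoppers, equal in both arms, scores 0 instead of 30.

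Difference = (0.30 − 0.15) × 30 × (1 − f) = 4.5 × (1 − f).

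| f | Control mean | Intervention mean | Difference (days) |
| --- | --- | --- | --- |
| 0 | 9.0 | 4.5 | 4.5 |
| 0.25 | 6.75 | 3.375 | 3.375 |
| 0.5 | 4.5 | 2.25 | 2.25 |
| 0.75 | 2.25 | 1.125 | 1.125 |
| 1 | 0 | 0 | 0 |

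**4. Other assumptions.** Let stopping count as 28 days, and let everyone else, and stoppers who answer for the remaining drug, miss 2 days on average. The difference is then 0.15 × (28 − 2) × (1 − f) = 3.9 × (1 − f): 3.9 days at f = 0, 1.95 at f = 0.5 and 0.78 at f = 0.8. The proportional loss is the same.

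**5. Unequal shares.** The shrinkage depends on f being similar in the two arms. With the inputs of step 3, f = 0.5 in control and 0 in intervention gives 0.30 × 30 × 0.5 − 0.15 × 30 = 0 days. The reverse gives 0.30 × 30 − 0.15 × 30 × 0.5 = 6.75 days, an exaggeration.

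**The case against.** **Question 1 already identifies stoppers.** Anyone who answers no for a starting class could be given a full month of missed days, whatever the answers to questions 2 and 3. This largely stands: most stoppers can be scored from data already planned. Two things cannot be recovered. Question 1 gives no stopping date, so someone who stopped within the last month would be mis-scored. It also says nothing about patients still on both classes who skip one.

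**Scoring belongs in a statistical analysis plan.** One may exist and is not shown, so the absence of a derivation rule would not by itself be a finding. But the Protocol sets the question wording and the endpoint definition, and no later plan can supply answers that were never asked for.

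**The lead-in names the therapy prescribed at the start.** That is a fair guide to what was intended, and it means a zero score is possible rather than certain. The phrase is not, however, part of the questions as listed, and it gives no scoring rule.

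**Stronger readings.** A reader might infer that the two primary endpoints contradict each other. They do not: they are different quantities, and two measures may diverge for one patient without either statement being wrong. A reader might also infer that stoppers will be left out of the missed-days analysis, leaving a group selected after randomisation. No section says so, and section 6.2 does not restrict the analysis. Nor does section 3.1 show that stopping one class only will be common. It says that most patients take both classes, not how they stop.

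**Conclusion.** The point holds as a measurement ambiguity in one of two listed primary endpoints. The Protocol does not say which regimen the missed-days count covers, its stopping rules do not extend to that count, and the questions cannot separate the classes. The same behaviour may therefore be scored as zero or as a full month.

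If stoppers answer only for the remaining drug at a similar rate in both arms, the difference in missed days is diluted in proportion to the share who do so: anywhere from 4.5 days down to 0 under the assumptions of step 3. That range is not an estimate of bias. The Protocol gives no figures for missed days or for the share stopping one class only. The illustration also takes background missed days as equal in the arms, although reminders might well change them.

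The continuation endpoint and the sample size of 300 are unaffected. The change should be made, but the point does not undermine the trial.

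**What to change.** In section 4.5, ask questions 2 and 3 separately for each class prescribed at the start. In section 5.1, state that:

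- a missed day is a day on which any starting class was not taken;
- days after stopping a class count as missed, with question 1 used to identify stoppers;
- all patients with follow-up data are included, whether or not they are still on treatment.

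The scoring text should also say how the two class counts are combined. Two counts place the number of days with any class missed only between the larger count and their sum (at most the whole month). For a class stopped before the month began, the larger count is already the full month and the choice does not matter.

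The cost is two extra questions on the follow-up form and one scoring sentence. No visit, sample or change in sample size is needed.
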